### Data analyses

Using the abdominal CT-scans, abdominal fat volumes will be segmented and quantified using a semi-automatic dedicated software (iNtuition, TeraRecon Inc. San Mateo, CA, USA) [20, 30]. This allows quantification of subcutaneous abdominal fat volume (SAV), visceral abdominal fat volume (VAV), total abdominal fat volume (TAV) and visceral fat percentage (VAV% = [VAV/TAV] x100). Hormone levels (locally in the adipose and tumour tissue and systemically in the blood) will be measured by Liquid-Chromatography-tandem-Mass-Spectrometry (LC-MS/MS) analysis and compared pre- and postoperatively. The biospecimens will be temporarily stored prior to use in this study at the MUMC Biobank [31]. In the Biobank Information System (BIS) type, date and volume of each specimen is recorded. A selection of steroid hormones including oestrogens, androgens, progestogens and corticosteroids as well as local adiponectin, resistin, leptin will be determined in the collected adipose tissue. Inflammatory markers both locally in fat tissue (macrophages, T cells: TNF-α, IL-6, and IL-1β) and systemically (blood) (including C-reactive protein (CRP), interleukin 1 beta (IL1β), interleukin 6 (IL6), tumour necrosis factor alpha (TNFα), insulin-like growth factor 1(IGF1)), will be determined. Samples will be further characterised by omics technologies (genomics, transcriptomics, proteomics and metabolomics). Generated data will be used for biomarker discovery, this data will be used to explore the cellular pathways underlying the various patient characteristics. Furthermore, we will analyse the effect of CT derived fat distribution markers on hormonal/inflammatory activity in different corresponding fat samples.

Pre- and postoperative questionnaires will be analysed and compared. The Green climacteric Scale, assessing menopausal complaints, can be divided into three subcategories; psychological, physical and vasomotor complaints [32]. We will assess all three subcategories separately to evaluate if there are any differences in the groups of patients (pre vs. postmenopausal and obese vs. non-obese patients).

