## Abstract

**Background:**

Obesity is a growing problem worldwide, especially in countries with improved socioeconomic circumstances. Also, in the Netherlands the incidence of overweight and obesity is rising. There is increasing evidence on the association between obesity and tumorigenesis. Of all cancer types, endometrial cancer (EC) has the strongest positive correlation with obesity. Obesity is generally defined as a body mass index (BMI) >30, yet does not cover the differences in fat distribution in visceral and subcutaneous compartments. Visceral fat is assumed to be relatively more metabolically active and likely negative prognostic biomarker in non-endometrioid EC. Whereas subcutaneous fat is mainly responsible for oestrogen production through increased aromatase activity.

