### Objective/aim

The aim of this study is to compare hormone levels and inflammatory markers after BSO in obese and non-obese patients. Secondary objectives are to compare the effect of fat distribution and diagnosis (benign vs. endometrial cancer) on changes in hormone levels and inflammatory markers after BSO in obese and non-obese patients, and to compare the effect of BSO on menopausal complaints. We hypothesize that obese post-menopausal women will still have relatively high circulating concentration of oestrogen, especially women with a high subcutaneous fat percentage.

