### Statistical analysis

Variables will be analysed quantitatively (CT derived markers, hormones and inflammatory markers) or qualitatively (menopausal symptoms) and stratified by menopausal status and BMI. Comparison of characteristics and study variables will be performed using Chi squared tests (categorical data) and Mann Whitney U test or student t-test (continuous variables, depending on normality of distribution). Correlations will be assessed using Spearman’s rank correlation. Study-related, the oncological patients will be followed for three years for disease recurrence and/or disease-related death. Additionally, correlations between inflammatory markers in adipose tissue and circulating oestrogen levels after treatment and outcome are observed.

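### The only association method named for the CT fat markers is bivariate, so it cannot separate subcutaneous from visceral effects if the two volumes are correlated within strata

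*Protocol article*

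**What the plan says.** All of this is in the protocol article.

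- **Roles of the compartments.** The abstract's Background says that "subcutaneous fat is mainly responsible for oestrogen production through increased aromatase activity", and describes visceral fat as the more metabolically active compartment.
- **Objective and hypothesis.** Under Objective/aim: "Secondary objectives are to compare the effect of fat distribution and diagnosis (benign vs. endometrial cancer) on changes in hormone levels and inflammatory markers". The hypothesis there is that oestrogen stays relatively high in obese post-menopausal women, "especially women with a high subcutaneous fat percentage".
- **Markers.** Data analyses lists the subcutaneous (SAV), visceral (VAV) and total (TAV) volumes and "visceral fat percentage (VAV% = [VAV/TAV] x100"), and adds that "we will analyse the effect of CT derived fat distribution markers on hormonal/inflammatory activity in different corresponding fat samples". That sentence names no test.
- **Methods.** Statistical analysis names chi-squared, Mann-Whitney U and t-tests for comparisons, with stratification by menopausal status and BMI. For association it says "Correlations will be assessed using Spearman’s rank correlation". The article names no partial correlation, regression or other mutually adjusted analysis.

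**The concern.** The scientific question is specific to a compartment: does subcutaneous or visceral fat account for the hormone and inflammation findings? All four CT markers are functions of the same two volumes. A bivariate coefficient for VAV measures the association of VAV together with everything that moves with VAV, including SAV. If larger SAV goes with larger VAV among women of the same BMI group and menopausal status, VAV will correlate with oestrogen even when only subcutaneous fat produces it. At stake is a visceral finding for oestrogen that merely reflects subcutaneous fat, or the reverse for inflammatory markers. This touches a secondary objective and leaves the primary lean-versus-obese comparison unaffected.

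**Working it through.** The plan gives no figure of its own on this point, so there is none to reproduce. The check asks how often a marker with no effect would be called significant.

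**Inputs from the article.** There are 160 women, 80 per BMI group, with menopausal status split evenly. Each BMI-by-menopause stratum therefore has 160 / 4 = 40. Alpha is 0.05, taken as two-sided.

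**Assumptions, not in the documents.** SAV and VAV are lognormal. Only log SAV acts on the outcome, with correlation b = 0.5. The within-stratum SAV–VAV correlation ρ is 0.4 to 0.8, with 0.2 also shown.

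**Step 1: correlation that VAV inherits.** On the log scale, r(VAV, outcome) = b × ρ. The matching Spearman value is r_s = (6/π) × arcsin(r/2).

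**Step 2: chance that Spearman calls VAV significant.** This is approximately Φ(d − 1.96) + Φ(−d − 1.96), with d = atanh(r_s) × √(n − 3). For n = 40, √37 = 6.08.

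| ρ | b × ρ | r_s | d | VAV falsely significant, n = 40 |
|---|---|---|---|---|
| 0.2 | 0.10 | 0.096 | 0.58 | 9% |
| 0.4 | 0.20 | 0.191 | 1.18 | 22% |
| 0.6 | 0.30 | 0.288 | 1.80 | 44% |
| 0.8 | 0.40 | 0.385 | 2.47 | 69% |

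Simulation agrees within its error. In a whole BMI group of 80 the range for ρ = 0.4 to 0.8 is about 39% to 94%. With a weaker effect, b = 0.4, the figure at n = 40 and ρ = 0.6 is about 29%. At ρ = 0 it is the nominal 5%.

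**Step 3: both volumes together.** The partial correlation of VAV given SAV is proportional to bρ − b × ρ = 0. The simulated rate for VAV is accordingly about 5% at every ρ.

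**Step 4: does the plan miss the SAV effect?** For SAV itself r_s = (6/π) × arcsin(0.25) = 0.483, so d = 0.526 × 6.08 = 3.20 and power is about 89% at n = 40 (simulated 88–89%). At n = 80 it exceeds 99%.

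**Step 5: price of joint entry.** The partial correlation of SAV given VAV is (b − bρ × ρ) / √[(1 − b²ρ²)(1 − ρ²)]. At ρ = 0.8 this is (0.5 − 0.32) / √(0.84 × 0.36) = 0.18 / 0.550 = 0.327. Then d = atanh(0.327) × √(40 − 4) = 0.340 × 6 = 2.04, and power is about 53%. At ρ = 0.6 it is about 77%.

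**Step 6: VAV%.** Under the same SAV-only model at n = 80 and ρ = 0.6, with typical VAV half of SAV (assumed), simulated power for VAV% depends on the log-SDs of SAV and VAV:

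| log-SD of SAV | log-SD of VAV | Power of VAV% |
|---|---|---|
| 0.35 | 0.60 | about 5% |
| 0.35 | 0.45 | about 15% |
| 0.35 | 0.35 | about 49% |
| 0.45 | 0.35 | about 79% |

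The documents give no SDs, so no general statement about VAV% follows.

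**The case against.** **The article does not say that each marker is tested alone, and adjusted models may be in an unseen full protocol or SAP.** This is fair. The one-marker-at-a-time reading is inferred, and a missing model would not be a finding in itself. What remains is that the article does name a method for association, and that method cannot answer the compartment question it poses.

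**Stratification already deals with it.** In part. It removes the correlation created by pooling lean and obese women. It does not remove correlation within a stratum, which is what the figures above describe.

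**Compartment attribution does not rest on CT and blood alone.** This also stands. Subcutaneous and visceral tissue are sampled and assayed separately, which gives independent evidence. It does not change what a VAV correlation with circulating hormones can show.

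**Stronger readings that the documents do not support.**

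- A reader might infer that a subcutaneous effect would be missed. It would not, because SAV is itself quantified and Spearman on SAV has at least the power of the joint model wherever the volumes are substantially correlated.
- A reader might infer that VAV% cancels a real effect and should be dropped. That depends on unstated spreads. VAV% also measures relative distribution, which is what the hypothesis is about: if the SAV:VAV ratio drives the outcome, VAV% is significant in over 99% of studies at n = 80 and 90% at n = 40. Nothing here obliges the authors to reword the hypothesis.
- A reader might take misattribution as certain. It depends on a SAV–VAV correlation that the documents do not give.

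**Conclusion.** The point holds in a limited form. The named method cannot distinguish subcutaneous from visceral effects if SAV and VAV are correlated within strata. If only SAV acts at 0.5, false visceral findings occur in about 22% to 69% of analyses in a stratum of 40 for correlations of 0.4 to 0.8, and in about 9% at 0.2. Joint entry gives about 5%. The size rests on the assumed effect and on the assumed SAV–VAV correlation, and it disappears if the volumes are uncorrelated. It concerns the interpretation of a secondary objective. It is not a reason to abandon Spearman's correlation or VAV%.

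**What to change.** Keep the Spearman correlations and VAV%. For the fat-distribution objective, add one mutually adjusted analysis: a linear model of the log outcome on log SAV and log VAV together, with BMI group and menopausal status as factors. The equivalent partial Spearman correlations would also serve. Report both slopes with 95% confidence intervals, and state that any conclusion specific to one compartment rests on this analysis.

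No new data are needed, since both volumes are already measured. The cost is wider intervals and less power for each compartment when the volumes are highly correlated: about 53% for the SAV term against 88% for Spearman on SAV at n = 40 and a correlation of 0.8. Fitting one model to all 160 women with the strata as factors would soften that loss, provided common slopes across strata are acceptable.

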### Stratification

We strive to include a safety margin of 5–10% per stratum to allow for missing data. In both cohorts, due to a short preoperative waiting list (<4 weeks) it is not expected any patients are included whose data or tissue is not subsequently used. For this study, we can optimally compare the included participants using our 20/20/20/20 distribution. Using a population-based inclusion, we would likely have too low numbers in some groups to allow for meaningful analyses. However, as a consequence the external validity is somewhat reduced.

### Statistical analysis

Variables will be analysed quantitatively (CT derived markers, hormones and inflammatory markers) or qualitatively (menopausal symptoms) and stratified by menopausal status and BMI. Comparison of characteristics and study variables will be performed using Chi squared tests (categorical data) and Mann Whitney U test or student t-test (continuous variables, depending on normality of distribution). Correlations will be assessed using Spearman’s rank correlation. Study-related, the oncological patients will be followed for three years for disease recurrence and/or disease-related death. Additionally, correlations between inflammatory markers in adipose tissue and circulating oestrogen levels after treatment and outcome are observed.

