### Participants (Fig 2)

**Fig 2 pone.0276516.g002:**
[figure not shown]
Schematic display of participants. Total number of participants is 160 women.

In total 160 patients will be included, of which 80 patients with a normal BMI between 18–25 kg/m2 and 80 obese patients with BMI ≥35 kg/m2 (WHO obesity class 2). In both these groups an even number of peri-/premenopausal women and postmenopausal women are included, and women with endometrial cancer (EC) and/or atypical endometrial hyperplasia; cases, and women with a benign adnexal pathology (including but not limited to adnexal enlargement/abnormality); controls will be included. Patients will be included pre-operatively. In case of a final diagnosis being ovarian malignancy, this participant will be excluded and a patient with a benign diagnosis included instead.

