### Sample size

There are no previous studies with comparable analysis, allowing for a formal sample size calculation. Therefore, we have taken the difference in hormone level as the starting point for a sample size calculation. Based on an expected difference of 20% in hormone level changes between lean and obese patients (decrease in hormone levels of 70% in lean, and 50% in obese after BSO), using a 90% power and alpha 0.05, 154 patients are required for the primary objective of this study [29]. We have chosen to include 160 women, 80 obese and 80 non-obese. The gap in BMI between the 2 groups (7/10 BMI points) increases the likelihood to obtain significant differences in hormone- and inflammation marker levels.

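### The 90% power belongs to one overall obese-lean contrast; the analysis text stratifies by menopausal status with unadjusted tests and does not say which comparison is primary

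*Protocol article*

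**What the plan says.** - **Sample size (Protocol article).** The planning effect is a "decrease in hormone levels of 70% in lean, and 50% in obese after BSO", and "using a 90% power and alpha 0.05, 154 patients are required for the primary objective of this study". The section goes on: "We have chosen to include 160 women, 80 obese and 80 non-obese". No allowance is made for tests within menopausal strata, and no SD is given.
- **Participants (Fig 2).** "In both these groups an even number of peri-/premenopausal women and postmenopausal women are included". That makes 40 and 40 within each BMI group of 80. The Stratification section confirms it with four cells of 20.
- **Statistical analysis.** Variables are analysed quantitatively "or qualitatively (menopausal symptoms) and stratified by menopausal status and BMI". Hormones are among the variables listed. The group tests named are chi-squared, Mann-Whitney and Student's t; correlations use Spearman's coefficient. No adjusted model or test that combines strata is named.
- **Objective/aim.** The main aim is framed as obese versus non-obese overall. The hypothesis then reads: "We hypothesize that obese post-menopausal women will still have relatively high circulating concentration of oestrogen".

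**The concern.** The article gives two descriptions of the central comparison and does not join them. The power statement concerns one contrast across all women. The analysis text describes work by menopausal status with simple two-sample tests, and none of these combines strata.

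Either way of resolving this has a cost. If the obese-lean test is run separately before and after menopause, it is not the test that was powered. If it is run on all women with the named tests, the factors on which the cohort was deliberately balanced are left out of the analysis. The Introduction itself says that the ovaries are the main oestrogen source before menopause and subcutaneous fat is after it, so the fall after surgery may well differ between the strata.

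Two separate stratum p-values would also invite the conclusion that the BMI effect differs by menopausal status, although no named test addresses that.

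**Working it through.** **Inputs.** From Sample size: falls of 70% and 50% (a difference of 20 points), alpha 0.05, power 90%, 154 required (77 per group), 160 planned (80 per group). From Participants and Stratification: 40 per BMI group in each menopausal stratum. Assumptions, because the article is silent: two-sided test, SD of the percentage change, and the same 20-point effect in both strata.

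**1. The plan's own figure.** 154 cannot be derived from the stated inputs.
- Read as proportions: n = [1.960·√(2·0.6·0.4) + 1.2816·√(0.21 + 0.25)]² / 0.20² = (1.358 + 0.869)² / 0.04 ≈ 124 per group, 248 in total. One-sided it is 202.
- Read as means: an SD is needed. Solving from 77 per group, d = (1.960 + 1.2816)·√(2/77) = 0.522, so SD = 20/0.522 ≈ 38.3 points. With the noncentral t, d = 0.526 and SD ≈ 38.0.

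The means reading is used below because it is the one that can be made to fit 154.

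**2. Overall contrast.** At d = 0.526, power is 90% at 77 versus 77 and 91% at 80 versus 80. A test that averages the two stratum differences keeps this: SE = 38.3·√(1/40) = 6.05, 20/6.05 = 3.30, power = Φ(3.30 − 1.96) ≈ 91%.

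**3. Separate test in one stratum, 40 versus 40.**

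| Reading | Power |
|---|---|
| Proportions, two-sided | 45% |
| Proportions, one-sided | 57% |
| Mann-Whitney (efficiency 0.955), SD 38 within stratum | 63% |
| t-test, SD 38 within stratum | 64% |
| Means, one-sided (implied SD 42) | 68% |
| t-test, SD 32.4 within stratum (step 4) | 78% |

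The two proportions rows come from a reading under which 154 itself falls short (72% two-sided at 77 per group). With 10% loss (36 versus 36), the t-test figure is about 60% at SD 38 and 73% at SD 32.4. Success in both strata has probability 0.641² ≈ 41% at SD 38 and 0.779² ≈ 61% at SD 32.4. At SD 38, 90% power in each stratum would take 4 × 77 = 308 women.

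**4. What adjustment gains.** Suppose instead that 38 is the SD over both strata together, and that the strata differ by D points in mean fall (assumption). With equal strata, within-stratum SD = √(38.0² − (D/2)²).

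| D | Within-stratum SD | Power, adjusted, 80 versus 80 |
|---|---|---|
| 20 | 36.7 | 93% |
| 30 | 35.0 | 95% |
| 40 | 32.4 | 97% |

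The unadjusted pooled test stays at 91%. SD 38 cannot be both the within-stratum and the total SD when D is not zero. The 64% therefore belongs with D = 0 and the 78% with D = 40.

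**5. BMI-by-menopause interaction of 20 points, 40 per cell.** SE = SD·√(4/40). At SD 38, SE = 12.0 and power is about 38%. At SD 32.4, SE = 10.2 and power is about 50%.

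**The case against.** The strongest reply is that the plan does not commit to separate stratum tests. BMI is named as a stratifier together with menopausal status, yet BMI is also the comparison, so the phrase may only mean that results are broken down by group. The aim and the sample size both speak of obese versus non-obese overall. This stands: a reader might infer that the study simply has 64% power, and the documents do not support that. The figure is conditional on testing within strata and on an SD that the article never states.

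A reader might also infer from the hypothesis that the primary test is limited to postmenopausal women. The text does not establish that. The hypothesis follows directly on text about changes after removal of the ovaries, and it defines no restricted primary comparison.

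It is also fair that even quotas balance menopausal status and diagnosis across the BMI groups. A pooled unadjusted test is then not confounded by these two factors; it gives up precision, by an amount that depends on an assumed gap between strata. An interaction test is not among the stated objectives. The exact model form and the scale of the outcome may properly sit in a full protocol or analysis plan that is not shown.

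What the reply does not remove is that the article does name its tests and its stratification. As written, these do not match the contrast it powers, and it does not say which comparison is primary.

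**Conclusion.** The point holds in conditional form. The 90% (91% at 160) applies to one overall contrast only. If the primary comparison is made within menopausal strata, power is below 90% on every reading tried: about 64% with SD 38 within strata, range about 45% to 78%. If it is pooled with the named tests, the balanced factors go unused, and adjustment would lift power from about 91% to 93–97% for a gap of 20–40 points between strata.

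All these figures rest on assumptions: an SD back-solved from 154, and a 20-point effect common to both strata. The gain from adjustment also rests on the assumed gap. The mismatch between the two sections does not depend on them. It is a clear and free improvement rather than a fatal flaw, since the overall comparison can keep its stated power.

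**What to change.** - **Primary analysis.** Name one model for the change in hormone level, fitted to all women, with BMI group, menopausal status and diagnosis as factors. Make the adjusted BMI contrast the single primary test.
- **Secondary, exploratory.** Report the BMI effect in each menopausal stratum with confidence intervals, and the BMI-by-menopause interaction. Say that a 20-point interaction would be found with only about 38–50% power, so that a difference between stratum p-values is not read as evidence of a different effect.
- **Power statement.** Say that the 90% applies to the overall contrast. State the SD assumed, and give within-stratum power as a range under that SD, not as a fixed 64%.

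The cost is wording in two sections. Menopausal status is recorded at the first time point and diagnosis already defines the groups. No extra patients or measurements are needed, and the article describes the study as still recruiting, so the change can be made before analysis.

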### Data collection schedule (Fig 3)

**Fig 3 pone.0276516.g003:**
[figure not shown]
Schematic display of content and timepoints (T) for data collection during the study period. Three time points for patients with benign disease (T1-T3) and four time points (T1-T4) for patients with endometrial cancer (EC).

At three (women with benign diagnoses) or four (women with EC) different time points data will be collected from the subjects.

At timepoint 1 (T1), a physical examination is conducted where hip and waist circumference are measured and patient variables including age, height, weight, BMI, history, cumulative illness rating scale (CIRS) and menopausal status collected. Furthermore, routine abdominal CT imaging will be performed in all patients. Finally, patients are requested to answer a validated questionnaire, the Green climacteric scale enquiring into presence of menopausal symptoms, and are asked to answer three questions on their physical activity level.

At timepoint 2 (T2) subjects will undergo the clinically indicated surgical procedure. At start of surgery, a fasting blood draw will be obtained to measure oestrogen levels and systemic inflammation markers. During surgery subcutaneous adipose tissue and visceral adipose tissue (fat apron and intestinal epiploic fat) as well as tumour (where applicable) will be collected, and snap frozen.

At timepoint 3 (T3) 4 to 6 weeks postoperatively, another fasting blood draw is obtained for measurement of oestrogen levels and systemic inflammation markers. In case of a recent infection the blood draw will be postponed until 10 days after the end of the infection. In case of adjuvant therapy, the postoperative blood draw will be performed latest at start of the adjuvant therapy. Finally, subjects will be asked to fill in the Green climacteric scale questionnaire a second time.

For subjects with the diagnosis of EC clinical follow-up data will be collected during 3 years (T4).

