Further, by including equally pre/ perimenopausal and postmenopausal women we can pin-point what effect the actual obesity has on the sex-steroid levels. An expected limitations will be that most women will be around menopausal age, because BSO may in specific very low risk situations be refrained from in women <45 years of age, balancing the risks of EC recurrence and iatrogenic menopause and is contra-indicated in women with a benign diagnoses.

Previous studies have found several clues for a relationship between obesity and endometrial cancer [5–7, 14]. We expect that our study will contribute to pinpoint the exact differences between ‘healthy obesity’ and ‘unhealthy obesity’ and will help to identify patients that are more at risk of developing cancer (or possibly suffer from other related problems such as cardiovascular problems e.g.).

Finally, our study will be able to relate the occurrence of menopausal complaints to BMI and fat distribution, which has not been previously addressed in in existing literature.

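### The lean-versus-obese comparison is controlled only by menopausal stratum and leaves recorded age unused, yet the Discussion claims to isolate the effect of obesity

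*Protocol article*

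**What the plan says.** All references are to the protocol article.

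- **Design.** Study design describes a prospective observational cohort. Participants and Sample size set 80 lean and 80 obese women. Each BMI group has equal numbers of pre-/perimenopausal and postmenopausal women, and both groups include cases (endometrial cancer or atypical hyperplasia) and benign controls. Stratification refers to a 20/20/20/20 distribution.
- **Data at T1.** Data collection schedule (Fig 3) lists "patient variables including age, height, weight, BMI, history, cumulative illness rating scale (CIRS) and menopausal status collected". Women also "are asked to answer three questions on their physical activity level".
- **Analysis.** Statistical analysis says that variables will be "stratified by menopausal status and BMI". It then gives the tests: "Comparison of characteristics and study variables will be performed using Chi squared tests (categorical data) and Mann Whitney U test or student t-test", the choice between the last two depending on normality. The only other method named is rank correlation: "Correlations will be assessed using Spearman’s rank correlation".
- **Claim.** The Discussion says that "by including equally pre/ perimenopausal and postmenopausal women we can pin-point what effect the actual obesity has on the sex-steroid levels".

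**The concern.** Lean and obese women are not randomised to their BMI group, so a difference between them can arise from anything that differs between the groups and also relates to the outcome. Recruitment fixes menopausal status, and the analysis stratifies by it. Age within a stratum is left free. The pre-/perimenopausal stratum is the clearest case: lean and obese women in it may differ in age and in the mix of premenopausal and perimenopausal women, and both plausibly bear on steroid and inflammatory markers.

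Under the stated tests, a difference produced by age would be reported as an effect of obesity, or could mask a real one. The Discussion raises the stakes because it rests an isolating claim on menopausal balance alone.

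**Working it through.** **1. The plan's own figure.** Sample size gives 154 patients for 90% power at alpha 0.05, with expected decreases of 70% (lean) and 50% (obese). No SD and no sidedness are stated.
- Read as two proportions, two-sided, this gives 124 per group, 248 in total, so 154 is not reproduced.
- Read as a difference of 20 points in means, 154 needs an SD of about 38.3: 20 × √(77/2) / (1.960 + 1.2816) = 38.3.

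This is a separate matter. Here 154 is taken at face value, two-sided, only to obtain a yardstick: d = (1.960 + 1.2816) × √(2/77) = 0.522 SD.

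**2. Assumed inputs (not in the documents).** Age imbalance between BMI groups δ = 0.25 to 0.5 SD. Within-group correlation of age with the outcome r = 0.2 to 0.4, taken as linear.

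**3. Bias of a comparison that ignores age.** Bias = δ × r.
- Low: 0.25 × 0.2 = 0.05 SD, which is 0.05/0.522 = 10% of the yardstick.
- High: 0.5 × 0.4 = 0.20 SD, which is 0.20/0.522 = 38%.

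**4. False-positive rate with no true obesity effect.** P(|Z + bias × √(n/2)| > 1.96), with n per group.

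| δ | r | Bias (SD) | 80 vs 80 | 40 vs 40 |
|---|---|---|---|---|
| 0.25 | 0.2 | 0.05 | 6.2% | 5.6% |
| 0.25 | 0.3 | 0.075 | 7.6% | 6.3% |
| 0.25 | 0.4 | 0.10 | 9.7% | 7.3% |
| 0.5 | 0.2 | 0.10 | 9.7% | 7.3% |
| 0.5 | 0.3 | 0.15 | 15.8% | 10.3% |
| 0.5 | 0.4 | 0.20 | 24.4% | 14.5% |

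The 40 versus 40 column is one menopausal stratum. Its rates are lower because the smaller sample detects the same bias less often. The bias in the estimate is the same for a given δ and r. To the extent that stratification shrinks δ, the upper rows become less likely.

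**5. Power if the bias opposes a true effect of 0.522 SD (80 vs 80).** Φ((0.522 − bias) × √40 − 1.96) falls from 91% without bias to 85% at bias 0.05 and 53% at bias 0.20.

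**6. After adjusting for age.** The sample-size factor is about (1 − r²)(1 + δ²/4).
- Smallest: (1 − 0.16)(1 + 0.0156) = 0.853, so 154 becomes 132.
- Largest: (1 − 0.04)(1 + 0.0625) = 1.02, so 154 becomes 158.

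Both lie within the planned 160 before any loss. Power at 0.522 SD with 80 versus 80 is 91% to 95%. A simulation with no true effect (4,000 runs, 80 versus 80) gave these false-positive rates, unadjusted against age-adjusted: 8.3% against 5.2% (δ 0.25, r 0.3), 15.4% against 5.2% (0.5, 0.3) and 25.8% against 4.6% (0.5, 0.4).

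**The case against.** **The article is condensed.** A covariate list is often left to the analysis plan, and the article does not say that its tests are the only ones. A reader might infer that no adjusted analysis exists anywhere. The text does not support that, since a fuller plan may hold one. What remains does not depend on silence: the article names its tests, and its Discussion draws a conclusion those tests cannot carry.

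**Age is not uncontrolled.** It is tempting to read the comparison as wholly unadjusted. That is too strong. Menopausal stratification and balanced recruitment remove part of any age difference. The Discussion expects most women to be near menopausal age, which narrows the range, and the planned comparison of characteristics could reveal an imbalance. These points reduce the problem, but none of them balances age between BMI groups within a stratum or corrects the estimate.

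**The outcome may be change.** Sample size is built on percentage decrease, and age may relate less to change than to level. This limits the likely size. It does not dispose of the point, because the stated aim is to compare hormone levels and inflammatory markers after surgery.

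**Physical activity.** Since it is collected, one might want it in the main model too. The documents do not support that. Activity may be a consequence of obesity, so adjusting for it could remove part of the effect of interest, and the article describes three questions with no scoring rule. The comorbidity scale (CIRS) raises the same difficulty.

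**The claim is one sentence.** Elsewhere the goal is to compare or explore differences, so rewording that sentence would meet much of the concern. It would not make use of the age data.

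**Conclusion.** The point holds in a limited form. The stated comparison controls for menopausal stratum but not for age within it, while the Discussion claims that menopausal balance is enough to isolate obesity. The stated method does not support the stated claim, and the plan should be changed.

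The size is unknown. Under the assumed inputs, false positives at a nominal 5% run from about 6% to 24% pooled and about 6% to 15% within one stratum. The low end is minor. The upper end takes no credit for whatever age imbalance stratification removes. These are illustrations and should not be read as a prediction of bias in this study. No calculation was made for physical activity.

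**What to change.** 1. **Statistical analysis.** Make the lean-versus-obese comparison of each hormone and inflammatory outcome a linear model, on the log scale where the outcome is skewed. Include BMI group, menopausal status, diagnosis and continuous age. Report the t-test or Mann-Whitney result beside it as the unadjusted companion.
2. **Sensitivity analyses.** Use physical activity and CIRS only here, and say that both may be consequences of obesity. State beforehand how the three activity questions will be scored.
3. **Discussion.** Replace the isolating claim with an association adjusted for menopausal status, diagnosis and age, and acknowledge that residual confounding is possible.

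**Cost.** The change is to wording only, because the data are already collected. Age takes one degree of freedom, and the interval widens slightly if age is strongly imbalanced and only weakly related to the outcome.
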